### Outcomes

#### Primary Outcome Measures

It is considered that the prevention of reoperation would be the most important clinically primary endpoint.

#### Secondary Outcome Measures

Secondary outcomes include clinical evaluation by the Markwalder score and radiologic characteristics of the CT/MR images over time. On axial CT scans the thickness of the hematoma and midline shift is measured in millimeters at the thickest area and the volume is calculated in cubic centimeters. Midline shift is measured at the level of the intraventricular foramen. Hematomas are classified as homogenous, laminar, separated or trabecular. Their location is classified as being over the convexity, at the cranial base or the interhemispheric space. There is also a focus on brain atrophy that is classified as none, mild, definite, or severe. Residual air is measured in cubic centimeters. The influence of a patient’s long-term medication is evaluated together with coexisting diseases as predictors for recurrence.

### Participant timeline

A time schedule of enrolment, interventions, assessments and visits for participiants are shown in Table 
2. The flow diagram (Figure 
1) illustrates the key steps of the trial.

**Figure 1 F1:**
[figure not shown]
Flow diagram.

### Sample size

Let p_verum_ be the reoperation rate in the verum group and p_placebo_ be the reoperation rate in the placebo group. The null hypothesis H_0_ is that the ratio of both rates p_placebo_ /p_verum_ is equal or smaller than 2, the corresponding alternative hypothesis H_1_ is that the ratio p_placebo_ /p_verum_ is larger than 2. In other words, the alternative hypothesis states that dexamethasone reduces the reoperation rate by 50% or more. For a reasonable medication the effect size is assumed to be this size because dexamethasone will be taken by the majority without benefit.

The assumed reoperation rate p_placebo_ is 10%. This is in accordance with the data from our department and the Chinese study sites. In order to detect a ratio p_placebo_ /p_verum_ of 2 or more with a power of 80%, the sample sizes are n1 = n2 = 370 in each arm. The type I error is 5% and the type II error for this scenario is 20%. The actual power of 83% is based on the exact power for the ratio of two binomial populations, one-sided and based on the score test (StatXact Cytel Software Corporation (2002) *StatXact 6.0 For Windows User Manual*, Cytel Software Corporation, Cambridge MA, USA). Due to possible drop-out of patients, we increased the sample sizes up to 410 in each group. Thus, 820 patients undergoing surgery for cSDH will be included.

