### Study objectives

#### Primary objective

The primary objective is to demonstrate that dexamethasone reduces the reoperation rate by 50% within 12 weeks after hematoma evacuation.

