### Data analysis

The primary endpoint is the rate of reoperation between 48 hours and 12 weeks after the initial evacuation of a chronic subdural hematoma. Mandatory reoperation during the first 48 hours is related to surgical complications. In such rare cases the patient will be excluded.

Evaluation of the Markwalder score will be done by computing crosstabulation tables and applying Pearson’s chi-square test. Data will be checked carefully for outliers and for normality based on the Kolmogrov-Smirnov test and Liliefors test. To evaluate the impact of dexamethasone on the thickness of the hematoma and other continuously distributed, metrically scaled variables, mixed models with treatment group as the independent factor and time as the repeated factor will be applied (if all assumptions for the model are met). Linearity will be assessed by Box Tidwell and log transformation. Corresponding planned contrasts together with 95% confidence intervals will be computed. If these variables do not fulfill the assumptions for parametric testing, nonparametric methods such as the bootstrap *t*-test, Kruskal-Wallis analysis of variance (ANOVA) with median tests and Friedman ANOVA with Wilcoxon matched-pairs test will be applied: 95% confidence intervals based on Pearson-Clopper values will be computed to estimate the reoperation rate in both groups. An unconditional test (Barnard’s test for superiority) for the ratio of these two proportions will be used. A *P*-value less than 5% will be considered statistically significant. All analyses will be done by one of the authors (WH) using STATISTICA 10 (Hill, T and Lewicki, P (2011). *STATISTICS: Methods and Applications*. StatSoft, Tulsa, OK, USA), StatXact 6.0 (Cytel Software Corporation (2003) Cytel Software Corporation, Cambridge MA, USA), NCSS 8 and PASS 11 Hintze, J (2012), NCSS 8, NCSS, LLC, Kaysville, UT, USA. (http://www.ncss.com).

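### The null hypothesis is written as a ratio of 2 or less, but the trial is powered at a ratio of exactly 2; the stated 83% belongs to a test of ratio 1

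*Protocol article*

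**What the plan says.** The Sample size section of the protocol article defines the hypotheses through the ratio of the placebo rate to the verum (dexamethasone) rate: "The null hypothesis H_0_ is that the ratio of both rates p_placebo_ /p_verum_ is equal or smaller than 2", and "the corresponding alternative hypothesis H_1_ is that the ratio p_placebo_ /p_verum_ is larger than 2". A further sentence puts the alternative into words as a halving of the reoperation rate or better.

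The same section assumes a placebo rate of 10% and takes as its target: "In order to detect a ratio p_placebo_ /p_verum_ of 2 or more with a power of 80" per cent. It arrives at 370 per arm with a type I error of 5%, raised to 410 per arm for drop-out. It adds: "The actual power of 83% is based on the exact power for the ratio of two binomial populations, one-sided", based on the score test.

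The Primary objective section agrees with the written hypotheses: "The primary objective is to demonstrate that dexamethasone reduces the reoperation rate by 50% within 12 weeks after hematoma evacuation". The Methodology section defends the 50% figure, arguing that with a smaller effect nearly all patients would take the drug without benefit.

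The Data analysis section names the primary test as an unconditional one (Barnard's "test for superiority) for the ratio of these two proportions will be used"), with the criterion that a P "value less than 5% will be considered statistically significant". It does not say which ratio is tested.

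**The concern.** A power statement is the probability of rejecting the null when a specified alternative is true. Here the effect used for planning, 10% against 5%, is not inside the alternative. It is the boundary point of the null, and a valid 5% test rejects there at most 5% of the time, whatever the sample size. The hypotheses and the 83% therefore cannot describe the same test. It appears that the effect to be detected has been entered as the null margin.

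Two things are at stake:

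- If the analyst tests the null as printed, a drug that works exactly as assumed will almost always be declared unproven.
- If the analyst tests a ratio of 1, a significant result shows only that the rate is reduced, while the objective and the worded alternative invite a report that a 50% reduction has been demonstrated.

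The Data analysis section does not give the null ratio, so the article does not settle which test decides the trial.

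**Working it through.** **Inputs, all from the Sample size section.** Placebo rate p_P = 0.10; design ratio 2, so verum rate p_V = 0.10/2 = 0.05; n = 370 per arm (410 with the drop-out allowance); one-sided α = 0.05, critical value 1.645; score test with exact power.

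**Statistic.** For null ratio R, with observed rates a (placebo) and b (verum):

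Z = (a − R·b) / √{ [p̃_P(1 − p̃_P) + R²·p̃_V(1 − p̃_V)] / n },

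where p̃_P = R·p̃_V are the maximum likelihood estimates constrained to the null. With R = 1 this is the pooled score test. Power is the sum of the two-binomial probabilities over all outcomes with Z > 1.645.

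**Step 1: reproduce the plan's figure, R = 1.**

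- Normal approximation: the pooled rate is 0.075. z = [0.05·√370 − 1.645·√(2·0.075·0.925)] / √(0.10·0.90 + 0.05·0.95) = (0.9618 − 0.6127)/0.3708 = 0.941, so power is 82.7%.
- Exact enumeration: 83.3% with the 1.645 cut-off, 82.6% with the exact unconditional cut-off.

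All three match the stated 83%. (The normal-approximation sample size for 80% is 343 per arm, so what is reproduced is the 83% at 370, not the choice of 370 itself.)

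**Step 2: the null as written, R = 2.** Exact enumeration with placebo rate 10% and one-sided 5%:

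| True verum rate | True ratio | Power, 370 per arm |
|---|---|---|
| 5% (design) | 2 | 4.8% |
| 4% | 2.5 | 17.7% |
| 3% | 3.33 | 46.9% |
| 2.5% | 4 | 65.7% |
| 2% | 5 | 82.6% |

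At 410 per arm and verum 5% the figure is again 4.8% (4.5% with the exact unconditional cut-off). A larger trial does not help at this point, because the rejection probability there is the type I error.

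**Step 3: what each null demands of the data.** Suppose 37/370 reoperations on placebo, the assumed 10%.

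- R = 1: 24/370 on verum gives Z = 0.03514/0.02022 = 1.74 (significant); 25/370 gives 1.59 (not). The cut-off is 24, an observed reduction of (37 − 24)/37 = 35%.
- R = 2: 10/370 gives Z = (0.1000 − 2·0.02703)/0.02552 = 1.80 (significant); 11/370 gives 1.57 (not). The cut-off is 10, an observed reduction of (37 − 10)/37 = 73%.

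From 11 to 24 verum events the two readings disagree. An observed halving would be 18.5 events, inside that band.

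**The case against.** The best defence is that nothing was miscalculated. The 83% is right for the ordinary superiority test, 370 per arm is adequate for it, and the word superiority in the Data analysis section suggests a null ratio of 1. That much stands: the defect is in the stated hypothesis, not in the computation. It does not remove the contradiction, because the 50% threshold is printed in symbols, repeated in words, made the primary objective and argued for under Methodology. Nor does the target of a ratio of 2 or more rescue the power claim, since power over that range is lowest at 2.

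It can also be said that 50% was a deliberate threshold of worthwhile benefit, so that the margin is intended and only the power is wrong. The document allows this reading, and the sponsor must choose.

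Some stronger inferences should be resisted:

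- *The trial cannot succeed if read literally.* The chance is about 5% at a ratio of exactly 2, and it rises for larger effects.
- *Power is really about 73%, because a P-value below 5% means a two-sided test.* The Sample size section says one-sided, and the 95% Clopper-Pearson intervals in the Data analysis section describe each arm's rate. They do not make the comparison two-sided.
- *The ratio will never be estimated.* A condensed article commonly leaves an interval for the ratio to an analysis plan, which is not shown here, so its absence is no fault.

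**Conclusion.** The point holds. The written null (ratio of 2 or less) and the stated power (80% target, 83% actual) belong to different tests. At the design effect of 10% against 5%, the probability of rejecting the written null is 4.8% with 370 or 410 per arm. The 83% is obtained against a null ratio of 1, one-sided 5%. With 37/370 on placebo, the choice of null decides the primary conclusion for any verum count from 11 to 24.

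These figures assume the plan's own 10% placebo rate, the score statistic it names and the one-sided 5% level. Using the exact unconditional cut-off changes them only slightly. That the margin is a slip is the likelier explanation, since the 83% fits a null ratio of 1, but it is an inference. Because this governs the primary hypothesis and the claim, it needs to be settled before unblinding.

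**What to change.** **Recommended route.**

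- Sample size: restate the null as placebo/verum ratio ≤ 1 against > 1, one-sided 5%, and describe the 50% reduction as the assumed effect, not the margin. Change the sentence that puts the alternative into words accordingly.
- Data analysis: state for Barnard's test that the null ratio is 1 and the level is one-sided 5%.
- Primary objective: reword it to say that dexamethasone reduces the reoperation rate. A significant result should not be reported as demonstrating a 50% reduction unless a confidence bound for the ratio supports that.

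This costs wording and a less ambitious claim. No extra patients are needed, and the 83% stands.

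**If a margin of 2 is really intended.** Keep the hypotheses, withdraw the 80% and 83% as power at a ratio of 2, and restate power at a larger assumed effect. With 370 per arm it is about 47% at a verum rate of 3% and 83% at 2%. The sponsor would then have to justify an effect of that size or revise the sample size, and give the null ratio of 2 in the Data analysis section.

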^7^At week 12 the patient will return to the hospital for documentation of his/her residence (e.g. home, rehabilitation centre etc.), any new hospitalizations or surgical procedures (directly or indirectly related to the cSDH) since the first hospital discharge, and to ensure that ongoing AEs/SAEs or new SAEs are followed up/documented. In case of reoperation the same procedure is performed at week 24.

^8^AEs reporting and follow-up: Reporting of all new AEs up to one day after study drug discontinuation; follow-up of ongoing AEs only thereafter.

^9^SAEs related to study-mandated procedures after signature of informed consent and before study drug administration.

^10^Serious adverse events still ongoing at the Study Completion visit must be followed until resolution or stabilization or until the event is otherwise explained. New SAEs occurring at any time after the 21-day follow-up period after study drug discontinuation may be reported to the Sponsor within 24 hours of the investigator´s knowledge of the event, if felt appropriate by the investigators.

Two regular follow-up visits are planned. At weeks 4 and 12 after the operation a CT scan and clinical investigation are performed. Only in the case of reoperation is another visit necessary as an outpatient at week 24.

Concomitant medications will be proton pump inhibitors, vitamin K and anticonvulsants as required. In addition participants will have to avoid traditional medicines (that is, plant-, animal- or mineral-based medicine, such as traditional Chinese medicine).

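### Reoperation after discharge is documented only through attendance at visits in the route the article describes, and the only stated answer to drop-out is more patients, which leaves selective loss of a hard endpoint open

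*Protocol article*

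**What the plan says.** **Endpoint.** Data analysis defines the primary endpoint as the rate of reoperation from 48 hours to 12 weeks after the first evacuation. The Methodology section stresses that it is simple and involves no surrogate.

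**How it is documented after discharge.** There are two regular follow-up visits, at weeks 4 and 12, plus one at week 24 for reoperated patients. Footnote 7 of Table 2 says: "At week 12 the patient will return to the hospital for documentation of his/her residence", and at the same visit new hospitalizations and surgical procedures since discharge are recorded. No telephone contact or record request is described.

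**Other safety routes.**
- New adverse events are recorded only until one day after study drug ends (footnote 8).
- New serious adverse events arising later than 21 days after the drug ends may be reported at the investigator's discretion (footnote 10).
- Brain hematoma is a waived serious event, entered only on the adverse event pages of the case report form (Waived SAEs).

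**Drop-out.** The Sample size section first derives that "the sample sizes are n1 = n2 = 370 in each arm" and then adds: "Due to possible drop-out of patients, we increased the sample sizes up to 410 in each group". It gives no rate and no breakdown.

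**Exclusion after randomization.** Under Concomitant care, a day-3 glucose above 300 mg/dl leads to exclusion from the trial. Under Data analysis, patients reoperated in the first 48 hours are excluded.

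**The concern.** Reoperation is a yes/no fact with a date. Establishing it needs neither a scan nor an examination. If it is learned only when the patient attends, a hard event takes on the missingness of a clinic measurement. The patients most likely to be absent include those reoperated elsewhere and those who have deteriorated, so absence may be related to the outcome.

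Extra patients replace lost information but not the particular patients who are lost. If loss differs between arms in a way linked to reoperation, the comparison among attenders is biased whatever the sample size. The glucose exclusion adds to this. A corticosteroid may raise glucose, so this removal may fall unevenly on the arms, although the reoperation status of those patients would still be obtainable.

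With event rates of 5% to 10%, a modest number of unknown outcomes is large relative to the effect.

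**Working it through.** **Inputs from the Sample size section:** placebo rate 10%; ratio 2, so 5% on dexamethasone; type I error 5%; test "one-sided and based on the score test"; 370 evaluable and 410 randomized per arm; stated power 83%.

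**1. The plan's own figure.** Full enumeration of the one-sided score test of equal rates, at 10% vs 5% with 370 per arm, gives 83.3% with the asymptotic critical value and 82.6% with an unconditional exact one. The stated 83% is reproduced. This takes equality as the null. The section words its null as a ratio of 2 or less, which is a separate matter.

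**2. Size of the allowance.** 410 − 370 = 40 per arm, and 40/410 = 9.8%. Over both arms this is 80 patients.

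**3. Size of the effect in events.**
- At 370 per arm: 37 − 18.5 = 18.5.
- At 410 per arm: 41 − 20.5 = 20.5.
- Ratios: 40/18.5 = 2.2 and 40/20.5 = 1.95.

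**4. Illustration under no treatment effect.** The loss patterns are assumptions; no figure in the article supports them. The true rate is 10% in both arms, so 41 reoperations per 410. If L patients per arm are lost and a fraction d of them were reoperated, the rate among completers is (41 − L·d)/(410 − L). For L = 40:
- d = 5%: (41 − 2)/370 = 10.5%
- d = 15%: (41 − 6)/370 = 9.5%
- d = 20%: (41 − 8)/370 = 8.9%

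| Lost per arm | d, placebo | d, dexamethasone | One-sided rejection rate |
|---|---|---|---|
| 40 | equal | equal | about 5% (4.9% to 5.0% for d = 5% or 20%) |
| 10 | 5% | 15% | 6.4% |
| 20 | 5% | 15% | 8.0% |
| 40 | 5% | 15% | 12.3% |
| 40 | 5% | 20% | 18.2% |

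**5. Illustration with a real effect (10% vs 5%).** Suppose 40 are lost per arm, with d = 20% on placebo and 5% on dexamethasone. Completers show (41 − 8)/370 = 8.9% and (20.5 − 2)/370 = 5.0%. Power falls from 83% to 68%.

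**6. How far a positive result would have to be pushed.** Start from 37 vs 18.5 events among 370 per arm and suppose the 40 missing placebo patients have 4 reoperations (10%). Significance (one-sided pooled z, 5%) holds with 8 of 40 missing dexamethasone patients reoperated (20%, p = 0.033). It is lost with 10 of 40 (25%, p = 0.059), against an assumed 5%.

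**7. Gain if status were known for all 410 per arm.** Power is 86.6% (asymptotic critical value) or about 86% (unconditional exact), so about 3 points more.

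**The case against.** Four points on the other side carry weight.

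- **A condensed article.** What a site does after a missed visit may be in the full protocol. The article does not say that attendance is the sole source. This stands as a limit on wording: it is the only route described. It does not remove the point, because footnote 7 fixes a return to hospital as the means, and the other routes shown are time-limited or discretionary.
- **Loss is partly contained.** A week 4 contact captures earlier events, the week 24 visit presupposes that sites learn of reoperations, and exclusion criteria 12 and 13 screen out patients known to be unable to have follow-up imaging or to return. This stands, but entry criteria cannot prevent later deterioration or surgery elsewhere.
- **The 40 per arm is an allowance.** A reader might infer that the trial plans to lose 80 endpoints, or expects a loss larger than its whole effect. The text does not support that. It speaks of possible drop-out and sizes up to 410, and the margin may partly cover glucose exclusions and 48-hour reoperations. The latter lie outside the endpoint window, so no telephone call would recover them.
- **The distortion needs strong assumptions.** The 12% to 18% figures use the whole allowance and a three- to four-fold difference in risk between lost patients of the two arms, in a double-blind trial. With smaller loss the effect is small, and with equal risk it is absent. This stands in full.

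Analysis populations and missing-data sensitivity analyses may sit in an analysis plan that is not shown, so their absence is not counted here.

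**Conclusion.** The point holds as a weakness in how the endpoint is collected. The described route ties a hard event to attendance, the only stated response to drop-out is a larger sample, and at least one group is removed after randomization for a reason that may depend on treatment. The allowance is about twice the expected difference in events, so strongly differential loss could create or hide an effect.

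The documents do not show that such loss is expected or likely. The false-positive range of 12% to 18% and the fall in power to 68% are illustrations resting on assumed loss patterns. A true result of the planned size would be overturned only if about a quarter of the missing dexamethasone patients had been reoperated, with missing placebo patients at 10%. The case for change rests on a cheap, avoidable risk, not on a demonstrated bias.

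**What to change.** In Table 2 and footnote 7, add one requirement. It covers every randomized patient who misses the week 12 visit, stops study drug, or is withdrawn after randomization, unless consent to follow-up has been withdrawn. For these patients, reoperation (yes/no, with date) and vital status at 12 weeks are obtained by telephone or from hospital records. State that these patients are included in the primary comparison. This concerns outcome collection only and leaves the treatment rules as they are.

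The contact should refer to the full 12 weeks. Table 2 prints 48±7 days for that visit, whereas 12 weeks is 84 days; the two must be reconciled.

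**Cost:** at most about 80 contacts if the whole allowance were used (2 × 40), plus a line in the consent form. Some tracing effort will fall on sites, and some patients will remain unknown.

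**Gain:** a lower risk of bias in the primary result, and up to about 3 points of power (83% to about 86%), fully realised only if status is obtained for all 410 per arm.

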### Randomization

Stratified randomization is done by using a computer randomization algorithm to generate balanced random samples (PASS 11, Hintze, J (2012). NCSS 8, NCSS, LLC. Kaysville, Utah, USA. http://www.ncss.com and Rosenberger, WF, and Lachin, JM 2002. *Randomization in Clinical Trials - Theory and Practice*. John Wiley & Sons. New York.) within each study site. Study site is the stratification variable for this randomization plan. Hence, the number of patients who receive verum medication is the same as the number of patients who receive a placebo in each study site, a 1:1 allocation ratio. Each patient receives a unique integer number ranging from 1 to 820 as an identification code, and this number will also be assigned to the corresponding medication kit. Each study site has a predefined set of patients to complete. In order to avoid consecutive recall of medication kits, the sequence in each study site is reordered by using random permutations.

The randomization plan will be implemented into an interactive web response system (IWRS) and hence the randomization is available for each study site. The investigators (or study staff) will interact with the system to receive the information as to which study group the patient is allocated, and which medication kit has to be used.

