### Trial design

This is a phase III, prospective, multi-center, double blind, randomized, placebo-controlled study. Eligible participants are randomized in a 1:1 allocation ratio to one of the two arms: an intervention arm, in which the participants receive dexamethasone according to the protocol, and a control arm in which they receive placebo.

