### Interventions

#### Investigational drug

The intervention which will be evaluated in this trial is the intake of dexamethasone. In Austria the tablets are provided in capsules of 4 mg each and are taken orally before 8.00 in the morning. The daily dosages are 16 mg at days 1 and 2, 12 mg at days 3 and 4, 8 mg at day 5, and 4 mg at day 6. In China there are only tablets of 0.75 mg dexamethasone available, so capsules are filled with six, four or three tablets. The following dosages can be obtained: 15.75 mg at days 1 and 2; 12 mg at days 3 and 4; 8.25 mg at day 5 and 4.5 mg at day 6. This intervention will be compared against placebo.

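### Randomisation is stratified by study site, but the only primary test named ignores site: a minor, low-cost mismatch that leaves the test valid and slightly conservative

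*Protocol article*

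**What the plan says.** - **Randomization:** allocation is stratified, and "Study site is the stratification variable for this randomization plan". Verum and placebo numbers are made equal within every site.
- **Data analysis, primary endpoint:** "An unconditional test (Barnard’s test for superiority) for the ratio of these two proportions will be used". For the rates themselves, "95% confidence intervals based on Pearson-Clopper values will be computed to estimate the reoperation rate in both groups". Neither statement mentions site.
- **Data analysis, secondary endpoints:** site is absent here too. For continuous outcomes, "mixed models with treatment group as the independent factor and time as the repeated factor will be applied"; the Markwalder score is analysed with Pearson's chi-square test on crosstabulations.
- **Sample size:** 370 per arm, a 10% placebo rate to be halved, one-sided, type I error 5%, exact power 83% from a score test for the ratio of two binomials. Dropout raises this to 410 per arm.
- **Setting:** sites lie in Austria and China. Under Investigational drug the article notes that "In China there are only tablets of 0.75 mg dexamethasone available"; the total dose is given as 68 mg in Austria and 68.25 mg in China.

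**The concern.** When allocation is forced to balance within a factor that predicts outcome, the true variance of the treatment difference contains only within-stratum variation. A test on the pooled 2x2 table still counts the between-site variation as noise. Its standard error is then too large and it rejects too seldom.

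Site could plausibly predict this endpoint. Reoperation is a decision taken by the local team, and the article describes no central adjudication of it. At stake is a little power and an analysis that does not match the design. The article does not leave the primary test open, so this concerns something it fixes rather than something it omits.

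**Working it through.** **1. Does the stated power come from an unstratified comparison?**

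Inputs from Sample size: n = 370 per arm, rates 0.10 and 0.05, one-sided alpha 0.05 (z = 1.645). The pooled rate is 0.075.

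- z_power = [0.05 × √370 − 1.645 × √(2 × 0.075 × 0.925)] / √(0.10 × 0.90 + 0.05 × 0.95)
- = (0.962 − 0.613) / 0.371 = 0.94, so power is 82.7%.

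Full enumeration of the two binomials gives 83.3% at the nominal critical value. With a Barnard-type critical value (1.685, which caps the maximum size at 5%) it gives 82.6%. The article's 83% is reproduced by a single pair of proportions with no strata, tested against a null ratio of 1. The two-sided version gives 73.4% and does not match. Site is therefore used in neither the sizing nor the analysis.

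**2. How conservative is the pooled test when sites differ?**

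Let s be the share of outcome variance that lies between sites:

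s = 1 − [mean of p(1−p) over sites] / [p̄(1−p̄)]

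Under no treatment effect the pooled statistic has variance 1 − s instead of 1, so its type I error is about 1 − Φ(1.645/√(1−s)). The site rates below are assumptions.

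- Half the sites at 5%, half at 15%: s = 1 − [(0.0475 + 0.1275)/2]/0.09 = 2.8%; 1.645/√0.972 = 1.668; type I error 4.8%.
- Half at 3.8%, half at 16.2%: s = 1 − [(0.0366 + 0.1358)/2]/0.09 = 4.3%; 1.645/√0.957 = 1.681; type I error 4.6%.
- Eight sites at 3.8% (35 per arm each) and two at 30% (45 per arm each): p̄ = 10.2%, s = 13.8%; 1.645/√0.862 = 1.772; type I error 3.8%.

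**3. Simulation of size and power**

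Assumptions: 10 sites, 370 per arm in total, rate halved in every site under the alternative, one-sided 5%, 200,000 trials per scenario. The pooled score test stands in for Barnard's test. CMH is the large-sample site-stratified test.

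| Assumed placebo rates by site | Size, pooled | Size, CMH | Power, pooled | Power, CMH |
|---|---|---|---|---|
| All 10% | 5.0% | 5.0% | 83.4% | 83.5% |
| Evenly from 5% to 15% | 4.8% | 5.0% | 83.4% | 83.6% |
| Half 3.8%, half 16.2% | 4.6% | 5.0% | 83.7% | 84.4% |
| Eight at 3.8%, two at 30% | 3.8% | 5.0% | 85.3% | 87.4% |

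The simulated sizes agree with step 2. The power gaps are 0.1, 0.2, 0.7 and 2.1 points. CMH holds its size with about 37 patients per arm per site.

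**4. Would an exact stratified test do as well?**

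Assumptions: 8 sites of 46 per arm, rate halved, 10,000 trials per scenario. Power of the exact conditional stratified test against the pooled score test:

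- Equal site rates: 79.7% against 83.1%, a loss of 3.4 points.
- Site rates 2% to 18%: 79.8% against 82.9%, a loss of 3.1 points.
- Sites at 5% and 15%: 80.7% against 83.8%, a loss of 3.1 points.

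A further simulation of the same layout gave 78% to 82% for the exact test, so about 2 to 5 points is a fair range. That is more than stratification gains in most of the scenarios in step 3.

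**The case against.** The strongest reply is that nothing the trial will conclude is at risk. The pooled test does not inflate type I error, and the 2-point end of the power loss needs an extreme pattern of sites. The 3.8% to 30% in the Background is a range across published series, not across this trial's centres. The Sample size section says the 10% rate agrees with data from the authors' own department and the Chinese sites, and Concomitant care standardises the operation. All of this stands, and it is why the point is minor. It does not show that individual sites are alike, and it does not remove the mismatch.

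A second reply is that Barnard's test is a sensible choice for two proportions. It is: at 82.6% it keeps nearly all the power of the score test, and it matches the unstratified sizing. That is a good reason to retain it as a sensitivity analysis.

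A third is that site adjustment may appear in an analysis plan that is not shown. It may, but a stratified primary test would depart from the one the article names.

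A reader might also infer more than the documents support:

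- **That the stratification is wasted.** It is not. Balance within sites remains a property of the design and guards the pooled comparison against confounding by site.
- **That the result would not hold across sites or countries, and that a stratified test would settle this.** A common ratio assumes consistency; it does not test it.
- **That the different tablets imply different reoperation rates.** Totals of 68 and 68.25 mg give no basis for that.

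**Conclusion.** The mismatch is real and lies in what the article states: randomisation stratified by site, primary test without site. Its size is minor. Under the assumed site patterns the pooled test's type I error is about 3.8% to 5.0%, and it gives up about 0 to 2 points of power, with essentially nothing lost when sites are alike. The figures rest on assumed numbers of sites, site sizes and site rates, none of which is in the text shown, and on a constant risk ratio across sites. The documents do not support reading the pooled test as invalid or anti-conservative.

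**What to change.** - Make the primary analysis a site-stratified large-sample Cochran-Mantel-Haenszel (score) test, reported with the common Mantel-Haenszel risk ratio and its confidence interval.
- Use the same null ratio as the primary hypothesis. The Sample size section writes a null of 2 or less, whereas its 83% reproduces only against a null of 1; that must be reconciled separately. The ordinary Cochran-Mantel-Haenszel test addresses a ratio of 1 only, so any other null needs the stratified score test for that ratio.
- Pool very small sites within country by a rule fixed before unblinding.
- Keep Barnard's test as a sensitivity analysis.
- Do not make the exact conditional stratified test primary.
- If consistency across sites, or between Austria and China, is to be claimed, pre-specify a separate heterogeneity check.

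If the sponsor prefers to keep Barnard's test as primary, the minimum is a stated reason and a pre-specified site-stratified sensitivity analysis.

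The cost is analysis-plan wording; no change to sample size or conduct is needed. The downsides are the pooling rule and reliance on a large-sample test in place of an exact one.
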